### Statistical methods

#### Power calculation

The study was powered to achieve a 25% reduction in HIV incidence among females aged 15–30 years old in the intervention arms. Using the AHRI’s actual HIV incidence data, we assumed HITS interventions were delivered in 2011 and simulated the effect of HITS interventions in 24 intervention communities after 3-years of follow up between 2012 and 2014. Using a simulation approach we then explored a scenario where the interventions lead to a 25% reduction in Arm 1 (micro-incentives), 25% reduction in Arm 3 (male-sensitive HIV specific counselling) and a 37% reduction in the combined arm (Arm 2) after 3-years of follow up.

The results (Fig. 5) show that we would have been able to detect this reduction in incidence in > 80% of simulation replicates (*p* < 0.05). Therefore, if we were to introduce the HITS intervention in 2018 and follow young females up for at least 3 years post-intervention (i.e. utilize a total of 17 years of incidence data – 2004 to 2021), we would be in excess of 90% power to detect such a reduction in incidence in this critical age-group.

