### Randomisation and blinding

Randomisation was performed by the trial statistician prior to intervention rollout to ensure that each arm has similar baseline HIV incidence rates among women aged 15 and 30 years. First, all 45 clusters were stratified by HIV incidence in young women using data from 7605 young women aged 15 and 30 years old, who were residents in the PIPSA between 2006 and 2015 at least for 1 year. A total of 34551 person years and 1636 seroconversion events have been recorded, yielding overall 4.7 new infections per 100 person years. Then the 45 clusters were divided into four strata according to their HIV incidence rate such that stratum 1 comprises clusters with the lowest incidence rate, while stratum 4 comprises clusters with the highest incidence rate. Each of Arm 1, 2, and 3 consists of two clusters from each of the four incidence stratum (thus a total of eight clusters per arm). Arm 4 (SoC) consists of five clusters from each of the incidence stratum 1, 2, and 4, and six clusters from incidence stratum 3 (thus a total of 25-clusters). The study is an open label trial.

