**Fig. 5 Fig5:**
[figure not shown]
Power calculations. Example of data simulations to determine sample size required to detect a 25% decrease in HIV incidence in females aged 15–30 years (in Arm 1 or 3 relative to the SoC arm) using the AHRI population-based HIV surveillance data (2004–2014)

In the total of 24 communities in the intervention arms, an estimated total of 4,667 individuals will receive a HITS intervention. In the 21 communities, an estimated 4,900 individuals will receive the standard-of-care.

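### The >80% and >90% power figures are tied by the Fig. 5 caption to Arm 1 or Arm 3 versus standard of care, but the article's own incidence data do not support them for that contrast

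*Protocol article*

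**What the plan says.** The Power calculation section states that the trial was sized for a "25% reduction in HIV incidence among females aged 15–30 years old in the intervention arms". It simulated 24 intervention communities, with incidence lowered by a quarter in each of the two single-intervention arms; the third arm was given "a 37% reduction in the combined arm (Arm 2) after 3-years of follow up". On follow-up in 2012-2014 it concludes, citing Fig. 5, that "we would have been able to detect this reduction in incidence in > 80% of simulation replicates". It then argues that with at least 3 years of follow-up from 2018, and 17 calendar years of incidence data in total, "we would be in excess of 90% power to detect such a reduction in incidence in this critical age-group".

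The prose does not say which comparison was tested in each replicate. Only the Fig. 5 caption does: a 25% decrease "in Arm 1 or 3 relative to the SoC arm".

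Randomisation and blinding supplies the only incidence data in the article: "A total of 34551 person years and 1636 seroconversion events have been recorded" among young women in 2006-2015. It gives eight clusters to each intervention arm. For standard of care it lists five clusters from each of three strata and six from the fourth, yet prints "thus a total of 25-clusters". The Abstract and the text under Fig. 5 give 21.

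**The concern.** HIV incidence in women aged 15-30 is a primary endpoint and the one used to size the trial. The Study design section sets out to compare two interventions, and the Statistical analysis section fits arm-by-period interactions, which give arm-specific effects. A reader will therefore take the power figures, as the caption invites, to apply to the voucher alone or EPIC-HIV alone against standard of care.

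On that reading, a null result for one arm would count as strong evidence against a 25% effect. If the true power is well below 80%, that inference is wrong.

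**Working it through.** **Inputs**
- Person-years and events, all 45 clusters: 34,551 and 1,636 (Randomisation and blinding). Rate = 1,636/34,551 = 4.735 per 100 person-years.
- Span: 2006-2015, read as 10 or 9 years. Assumption: person-years spread evenly over years and clusters.
- Clusters: 8 per intervention arm; standard of care 5 + 5 + 6 + 5 = 21.
- Effects: rate ratio 0.75 (Arms 1 and 3), 0.63 (Arm 2).
- Follow-up: 3 years as simulated. The planned window is at most about 3.9 years (February 2018 to December 2021); 4.0 is used as a generous limit.
- Two-sided alpha 0.05; the article does not state sidedness.

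**The stated figures.** The person-years and between-cluster variation behind the 2012-2014 simulation are not given, so it cannot be rerun. The check asks whether the published data can reach its result.

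**Events per cluster**
- 10-year span: 34,551/10/45 = 76.8 person-years a year; × 3 × 0.04735 = 10.9 events in 3 years.
- 9-year span: 34,551/9/45 = 85.3 person-years a year; 12.1 events in 3 years.

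**Single arm versus standard of care, 3 years, no clustering.** Power = Φ(|ln RR| / √(1/E1 + 1/E0) − 1.96).
- 10-year span: E1 = 8 × 10.9 × 0.75 = 65; E0 = 21 × 10.9 = 229; SE = 0.140; 0.2877/0.140 = 2.05; Φ(0.09) = **53.7%**.
- 9-year span: E1 = 73, E0 = 255; SE = 0.133; z = 2.16; Φ(0.20) = **58.1%**.

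**Variants of the single-arm contrast**

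| Variant | Power (10-year to 9-year span) |
|---|---|
| Schoenfeld, allocation 8/29, 3 years | 60-64% |
| Wald with 25 standard-of-care clusters, 3 years | 55-60% |
| Wald, 3.9 years | 65-69% |
| Wald, 4 years | 66-71% |
| Schoenfeld, 4 years | 72-77% |
| Difference-in-differences, 14 baseline years, 3 years | 47-52% |
| Wald, assumed between-cluster CV 0.15, 3 years | 47-50% |
| Wald, assumed between-cluster CV 0.25, 3 years | 38-40% |

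The CV rows add CV² × (1/8 + 1/21) to the variance; the CVs are assumptions. No two-sided single-arm row reaches 80%. By Wald, 80% would need about 5.1-5.6 years of follow-up, or an incidence of about 8-9 per 100 person-years at 3 years. For 90% it would need about 6.8-7.5 years.

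**Pooled contrast: 24 clusters at rate ratio 0.75 versus 21, no clustering**
- 3 years: 196 vs 229 events, SE 0.097, z = 2.96, **84%**; 9-year span **88%**.
- 3.9 years: 255 vs 298 events, SE 0.085, z = 3.37, **92%**; 9-year span **95%** (94.5%).

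With reductions of 25/25/37%, the pooled rate ratio is (16 × 0.75 + 8 × 0.63)/24 = 0.71 and 3-year power is 93-96%. Arm 2 alone at 0.63 gives 87-90% by Wald.

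**The step from >80% to >90%.** Take the difference-in-differences variance as proportional to 1/follow-up + 1/baseline and start from exactly 80% at 3 years. Extending the baseline from 8 to 14 years at unchanged follow-up gives an SE ratio of √[(1/3 + 1/8)/(1/3 + 1/14)] = 1.064, and Φ(2.80 × 1.064 − 1.96) = 85%. Lengthening follow-up as well gives 89% at 3.5 years and 91% at 3.9 years (90% and 92% from a 7-year starting baseline).

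**The case against.** The strongest reply is that the prose never ties either figure to a single arm. It speaks of the intervention arms and of 24 intervention communities, and the pooled calculation reproduces both figures closely. The single-arm wording is a parenthesis in the caption of a figure described as an example. This stands as far as it goes: the authors may well have run a pooled or any-arm test. But the prose cites Fig. 5 as its evidence, and the caption is the only place that names a contrast, so the published claim is still the single-arm one.

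The caption could also mean that either Arm 1 or Arm 3 is significant. That gives 75-79% at 3 years and 86-89% at 4 years without clustering, still short of the stated levels and not power for a named intervention.

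The inputs are also not the simulation's own. They come from the stratification dataset, restricted to women resident for at least a year, and spread evenly by assumption. This limits precision. It would not plausibly close the gap, since 80% at 3 years needs nearly double the stated incidence.

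Sidedness is not stated either. One-sided single-arm power is 66-75% at 3 years; only by Schoenfeld with about 3.9-4 years does it pass 80% over both spans (81-85%).

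Two stronger readings are tempting, and the documents support neither:
- That 54-58% is a ceiling. It is not: other formulas give more, and planned follow-up is at least 3 years, not exactly 3.
- That the rise to >90% is impossible because extra baseline years add no post-intervention events. The longer window to the end of 2021 can account for it from an 80% start, so the step is not disproved. What is weak is explaining it by the 17 years of data.

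**Conclusion.** The power statement does not hold for the contrast named in the Fig. 5 caption. For Arm 1 or Arm 3 versus standard of care and a 25% reduction, two-sided power before clustering is about 54-58% at 3 years by Wald (60-64% by Schoenfeld) and about 65-77% by the end of 2021. An assumed CV of 0.15-0.25 takes the 3-year Wald figure to about 38-50%. The stated figures match a pooled comparison of all 24 intervention clusters, and even that match ignores clustering.

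These values rest on evenly spread person-years, a constant 4.7 per 100 person-years, and the stratification data standing in for the simulation's inputs. They show that the claim and the caption do not fit together; they do not show that the simulation was wrongly run. Separately, the printed total of 25 standard-of-care clusters is an addition error for 21. It does not affect the conclusion.

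**What to change.** - State which contrast and test each simulation replicate used, and make the Fig. 5 caption agree with the text.
- Stop claiming more than 80% or 90% power for Arm 1 or Arm 3 versus standard of care.
- Report power separately for the single-arm, combined-arm and pooled contrasts. Take the figures from the trial's own simulation, with between-cluster variation and the actual follow-up window. The values above are checks and should not be copied into the protocol.
- Do not attribute the rise to >90% to the extra pre-intervention years alone; state how much comes from longer follow-up.
- Correct the standard-of-care total in Randomisation and blinding to 21.

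The cost is a less favourable stated figure for the single-arm contrasts. The change is to the text, supported by a further run or summary of the existing simulation, and needs no extra participants.

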**Fig. 5 Fig5:**
[figure not shown]
Power calculations. Example of data simulations to determine sample size required to detect a 25% decrease in HIV incidence in females aged 15–30 years (in Arm 1 or 3 relative to the SoC arm) using the AHRI population-based HIV surveillance data (2004–2014)

In the total of 24 communities in the intervention arms, an estimated total of 4,667 individuals will receive a HITS intervention. In the 21 communities, an estimated 4,900 individuals will receive the standard-of-care.

#### Statistical analysis

All primary analyses (both primary and secondary endpoints) will be intent-to-treat (ITT). For the binary primary outcomes – HIV testing uptake and HIV treatment linkage – we will use generalized linear models with Poisson distribution, log link function, and robust error terms to determine effect sizes (risk ratios). We will fit beta regression models for incidence and mortality rates [30, 31]. We will also adjust for both baseline endpoints and clustering through random effects. Under the difference-in-differences study design, the individuals are followed in two periods of time: the “before” and the “after” period, where the interventions occur in the “after” period [32]. The goal of the statistical analysis is to estimate the average treatment effect for the treated clusters (week blocks). We will make the usual assumption of parallel trend, that is, on average, the outcomes for all the clusters in the four arms would have followed a parallel path over time in the absence of the intervention [33]. Our generalized linear models will include fixed effects for the “before” and the “after” time periods, the grouping of the clusters in four arms, and the interaction between time periods and arms.

For the two survival-analytic primary endpoints – population-level mortality among men and population-level HIV incidence among women – we will use the Cox proportional hazards model to determine effect sizes (hazard ratios). If the proportional hazards assumption of the Cox model is violated, we will use appropriate alternative survival analytic models. We will use data from the period 2004–2017 for baseline endpoint adjustment. In addition, to the ITT analyses, we will measure intervention effects adjusted for non-compliance using instrumental variable (IV) approaches.

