### Study setting

The trial is conducted in the Hlabisa sub-district of the uMkhanyakude district located in northern KwaZulu-Natal South Africa between 2018 and 2021 (Fig. 2). The area is predominantly rural and has recorded one of the highest population HIV prevalence estimates globally [20]. In this sub-district, AHRI has one of the largest population-based Demographic and HIV surveillance since 2000. The surveillance covers 432 km^2^ geographic area over approximately 100 000 individuals and 60 000 residents at any given time. Trained field-workers visit all households in the surveillance area and interview a key resident informant annually. The household survey records demographic components of households including size, composition, fertility, migration, mortality, and nuptiality. The HIV surveillance is annually conducted on all resident individuals aged 15 years or older to collect sexual behaviour and general health data and dried blood spots (DBS) samples for anonymized HIV testing [21]. The fieldwork visits are carried out in systematic cycles of 45 "week blocks". A week block is a workload-equivalent area developed using a GPS based methodology [22]. AHRI works closely with the local Department of Health in a comprehensive HIV Treatment and Care Programme, decentralized to the 17 primary health care clinics in the sub-district. HIV testing and treatment are available at all 17 primary health care clinics and the district hospital. Since 2017, AHRI has introduced home-based rapid HIV testing as part of the annual HIV surveillance.

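### A randomised comparison is analysed as a difference-in-differences: the parallel-trend assumption is unnecessary and the estimate is less precise than baseline adjustment would give

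*Protocol article*

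**What the plan says.** All points are from the protocol article.

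- **Allocation** (Randomisation and blinding): "Randomisation was performed by the trial statistician prior to intervention rollout to ensure that each arm has similar baseline HIV incidence rates" (the group meant is young women). The 45 clusters were first divided into four incidence strata.
- **Design of the analysis** (Statistical analysis): "Under the difference-in-differences study design, the individuals are followed in two periods of time", before and after the interventions. The stated goal: "estimate the average treatment effect for the treated clusters (week blocks").
- **Identifying assumption**: "We will make the usual assumption of parallel trend, that is, on average, the outcomes for all the clusters in the four arms". The sentence then posits parallel movement without the intervention.
- **Model**: the generalized linear models have fixed effects for period, for "the grouping of the clusters in four arms, and the interaction between time periods and arms". The interaction carries the treatment effect, and the arm means before the intervention are left free.
- **Baseline**: "We will also adjust for both baseline endpoints and clustering through random effects". For the survival endpoints, "We will use data from the period 2004–2017 for baseline endpoint adjustment". The sentences on the Cox model do not mention DiD.
- **Errors**: robust error terms are named for the two binary outcomes, testing uptake and linkage. The article does not say whether they are computed at cluster level.
- **Length of the before period for testing** (Study setting): "Since 2017, AHRI has introduced home-based rapid HIV testing as part of the annual HIV surveillance". Delivery of the interventions began in February 2018 (Trial status).

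**The concern.** DiD with parallel trends is designed for settings where groups were not randomised and may differ at baseline. Here randomisation already makes the post-period arms comparable, so the plan rests its main comparison on an assumption it does not need.

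The period-by-arm interaction is also a change-score analysis. It subtracts the whole baseline difference between arms, giving the baseline a coefficient of 1 however weakly it predicts the outcome. Where the baseline is noisy, that noise passes into the treatment effect. With only eight clusters in each intervention arm, avoidable variance is costly. Testing and linkage are the most exposed because their before period is about one round. Stratification was on incidence in young women, so it does not directly balance men's earlier testing.

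A second issue is the sentence on adjusting for baseline endpoints. It can be read as adding the baseline as a covariate to a model that already holds it as outcome rows. That should be ruled out.

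**Working it through.** **Plan's own figures.** 1636 seroconversions / 34551 person-years = 4.735 per 100, matching the stated 4.7. The stated power (above 80%, then above 90%) comes from a simulation whose between-cluster variance and fitted model are not given, so it cannot be reproduced and cannot show which estimator was used.

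**1. General comparison.** Let v0 and v1 be the variances of a cluster's before and after values and c their covariance. Per cluster:
- DiD variance: v0 + v1 − 2c
- ANCOVA variance: v1 − c²/v0
- Difference: (v0 − c)²/v0, which is never negative

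DiD matches ANCOVA only if the regression slope c/v0 is exactly 1. This ignores the small cost of estimating one slope.

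**2. Equal variances in both periods.** The ratio DiD/ANCOVA becomes 2/(1+r). The ratio of DiD to a post-only analysis that ignores baseline is 2(1 − r).

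| r (assumed) | DiD/ANCOVA variance | SE larger by | DiD/post-only variance |
|---|---|---|---|
| 0.2 | 1.67 | 29% | 1.6 |
| 0.5 | 1.33 | 15% | 1.0 |
| 0.8 | 1.11 | 5% | 0.4 |

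Below r = 0.5, DiD is worse than not using the baseline at all.

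**3. Testing uptake, illustration.** Assumed, not in the article: 117 men per cluster, 25% uptake, between-cluster SD 0.3 on the logit scale, different men in each round.
- Sampling variance of a cluster logit: 1/(117 × 0.25 × 0.75) = 0.046
- Share of variance that is true cluster variation: 0.09/(0.09 + 0.046) = 0.66
- Underlying correlations of 0.3, 0.6 and 0.8 therefore become observed r of about 0.20, 0.40 and 0.53
- Variance ratios 2/(1+r): about 1.67, 1.43 and 1.31

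The formula takes the observed r, not the underlying correlation.

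**4. Incidence, if DiD were applied.** I assume the 34551 person-years span ten calendar years (2006–2015) and the rate is constant. I take 21 standard-of-care clusters, since the stratum counts 5 + 5 + 6 + 5 sum to 21.
- Follow-up events per cluster: 34551/10 × 3/45 = 230 person-years; × 0.04735 = 10.9
- Baseline events per cluster over 14 years: 34551/10 × 14/45 × 0.04735 = 50.9
- v1 = k² + 1/10.9, v0 = k² + 1/50.9, c = k² × the between-period cluster correlation
- Over between-cluster CV k = 0.1–0.3 and correlation 0.5–1.0, DiD/ANCOVA runs from 1.03 to 1.23

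Example, k = 0.2 and correlation 0.8: v1 = 0.1317, v0 = 0.0596, c = 0.032. DiD = 0.1273 and ANCOVA = 0.1145, ratio 1.11. For Arm 1 against standard of care (8 v 21 clusters, 25% reduction), approximate power is 0.49 with DiD, 0.53 with ANCOVA and 0.48 post-only. No allowance is made for stratification on incidence, which would tend to narrow the gap.

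**5. Baseline as both outcome row and covariate.** Standardise both periods to variance 1 in a random-intercept model.
- Pooled slope on baseline: (1+r)/2
- Within-cluster residual covariance: −(1−r)²/4, which is negative, so the cluster variance is estimated at zero
- Pooled residual variance: (3+r)(1−r)/4
- Model-based variance of the interaction is proportional to (3+r)(1−r)/2; the true variance to 2(1−r). Ratio (3+r)/4
- Model SE / true SE: 0.89, 0.935 and 0.975 at r = 0.2, 0.5 and 0.8

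A simulation of this linear model left the interaction estimate unchanged when the covariate was added, so it bought no precision. Type I error was 10.0%, 7.8% and 5.5%, against 6.3%, 5.4% and 5.1% for ANCOVA (z tests).

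**The case against.** **Randomisation makes parallel trends true in expectation.** This stands. A reader might infer that the planned estimate is biased, or that the assumption is likely to fail; the article supports neither. The assumption is redundant.

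**The baseline may not be used twice.** The adjustment sentence comes just before the description of the before/after design and may simply be describing it. This also stands. A reader might infer that the planned tests are anti-conservative, but the article does not clearly specify that model, and step 5 concerns model-based errors. For testing and linkage the plan names Poisson models with robust errors. A simulation of that model with cluster-robust errors and a t reference (step 3 inputs, 2,000 replicates per setting) gave type I error of 6.2%, 6.7% and 6.6% without the extra covariate and 6.0%, 6.5% and 6.4% with it, so the covariate added no inflation. Post-only Poisson ANCOVA with the same kind of errors gave 7.9%, 7.4% and 8.4%. The excess is a few-cluster problem that the remedy shares and must deal with.

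**For incidence and mortality the plan is already close to the remedy.** Largely right: the Cox sentences mention only baseline adjustment. A reader might infer a serious loss of power for incidence, but even under DiD the loss is modest with a long baseline.

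**The correlations are assumed, and following the same people would raise r.** True, and it would shrink the loss. It would not reverse the direction.

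**Conclusion.** The point holds as one of efficiency and clarity. The plan gives a randomised comparison an unneeded identifying assumption and an estimator whose variance is never below that of baseline adjustment, apart from the cost of one slope. With equal period variances the excess is 67%, 33% or 11% at r = 0.2, 0.5 or 0.8. It matters most for testing uptake and linkage; for incidence it is 3–23% and conditional on DiD being used. These sizes rest on assumed correlations and between-cluster variation, because the article gives neither.

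No bias is shown. Understated standard errors would arise only if the baseline were entered both as outcome rows and as a covariate and the errors were model-based rather than cluster-robust. The wording should exclude that, but does not establish it. The change is worth making because it costs almost nothing.

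**What to change.** Make the primary analysis a comparison of post-intervention outcomes, with:
- arm and randomisation stratum;
- the cluster's own baseline value as a covariate: the 2017 round for testing and, where available, for linkage; the log 2004–2017 rate for incidence and mortality. Availability for linkage needs checking, since one-year windows for men testing positive in 2017 run into the 2018 delivery period;
- inference that accounts for clusters, with a small-sample correction, given eight clusters per intervention arm.

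Drop the parallel-trend assumption from the primary analysis. Report DiD as a sensitivity analysis, and state that no further baseline covariate is added to it. Reword the adjustment sentence to say how the baseline enters each model.

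Cost: a change of wording, using data already held. The baseline covariate takes one degree of freedom, and the four-level stratum three if entered as categories, out of 45 clusters.
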